### Adherence

Participants in the intervention group will use the WeChat MiniApp to log in and complete the intervention sessions according to the schedule. The completion of each session will be tracked by “GDM ASCVD.” The “clock-in” function in the “GDM ASCVD” app will provide positive and constructive feedback to participants to enhance adherence. Participants will be able to “clock in” from the dashboard to track their exercise and eating habits on a regular basis.

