### Outcomes

#### Primary outcome measures

The primary endpoint is the percentage of fasting blood glucose, which is defined as the percentage of blood glucose levels within a normal range [17]. Glucose monitoring data is collected twice weekly after enrollment [time frame: from randomization (day 0) to V5 (week 12) for a total of 3 months of treatment]. The selected examination days shall be at least 2 days apart. Each examination day should contain the following self-monitoring data.

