#### Secondary outcome measures

1) The percentage of blood glucose levels collected within the normal range on each selected examination day.2) Loss of self-monitoring rate.3) HbA1c.4) Mean score of Diagnostic and Statistical Manual of Mental Disorders (DSM-5) assessment. DSM–5 is developed as a standard classification system for mental disorders. It provides a guideline of structured clinical interviews utilized to diagnose depression [18]5) Mean score of General Self-Efficacy Scale (GSE). The GSE is a psychometric scale that measures the confidence in one’s capacity to deal with a wide range of life’s issues. The test consists of ten items that describe attitudes toward barriers and are assessed on a scale of 0 (least optimal) to 4 (very optimal). A version in Chinese translation has been approved [19]6) Any insulin dose prescribed.7) Case number of low-birth-weight neonates. Low birth weight is defined as the first weight recorded after the birth of less than 2500 g (up to and including 2499 g) [20]8) Case number of neonatal macrosomia. Neonatal macrosomia is defined as the first weight recorded after the birth of more than 4000 g (more than and including 4000 g) [21].9) Hypoglycemic events in neonates (blood glucose < 2.2 µmol/L).10) Other fetal adverse events.11) Case number of GDM comorbidity developed during the intervention period.12) Case number of cesarean delivery.13) Total expenditures for delivery.

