### Statistical methods

#### Statistical methods for primary and secondary outcomes

Categorical variables will be expressed in numerical values with their respective percentages and compared using the chi-squared test at baseline. Continuous variables will be expressed as mean ± SD and compared using the *t*-test. The significance of primary and secondary endpoints will be evaluated with the paired-samples *t*-test. A *p*-value < 0.05 indicates statistical significance. All data will be analyzed with the SPSS.

All patients who have received CBT for at least 4 weeks will be included in the full analysis set (FAS). Depending on the time investigated, the per-protocol (PP) analysis set will be made up of patients who complete the 6-month follow-up examinations. The FAS will be used as the basis for the primary analysis. If there is a discrepancy of greater than 10% between the FAS and PP samples, the analysis will be repeated for the PP analysis set. The safety population will include patients in the FAS. Unless otherwise noted, all analysis will be done in both the FAS and PP analysis sets. No additional analysis will be conducted.

There will be no replacement or imputation of missing values. All analysis will be based solely on observed cases. Patients who loss to follow-up will be considered to have dropped out of therapy. Only the PP patients will be used in a sensitivity analysis to test the impact of this assumption.

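### The only missing-data check keeps completers alone, so it cannot test how women lost to follow-up are handled, and the same observed-case rule leaves missed glucose readings unexamined

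*Protocol article*

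**What the plan says.** The relevant rules are in the protocol article under *Statistical methods for primary and secondary outcomes*.

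- Missing values: "There will be no replacement or imputation of missing values. All analysis will be based solely on observed cases".
- Women lost: "Patients who loss to follow-up will be considered to have dropped out of therapy".
- The check on this: "Only the PP patients will be used in a sensitivity analysis to test the impact of this assumption".
- The set used for the check: "the per-protocol (PP) analysis set will be made up of patients who complete the 6-month follow-up examinations".
- Anything further: "No additional analysis will be conducted".

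The primary endpoint (*Primary outcome measures*) is the percentage of self-monitored readings in the normal range, with two examination days a week from randomisation to week 12. On the choice of days it says "The selected examination days shall be at least 2 days apart". The secondary outcomes include "Loss of self-monitoring rate". *Sample size* plans for 20% attrition and a 10-point difference. *Data collection* lists baseline, days 1, 14, 28, 56 and 84, and day 42 post-partum. It adds that missing data found in the EDC lead to a telephone call to the participant.

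**The concern.** Two kinds of missing data fall under one rule, and neither is examined.

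The first is women who are lost. Classing them as having dropped out of therapy gives them no outcome value. They contribute whatever they recorded before loss, or nothing. That is harmless only if their unseen results resemble those of the women who stayed. An analysis restricted to women who stayed cannot say whether they do.

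The second is single missed readings among women who remain. Because the endpoint is a ratio, a missed reading disappears from numerator and denominator together. If women skip or fail to record a test more often when glucose is likely to be high, the observed percentage is too favourable. If this happens to a different degree in the two arms, the treatment comparison is biased.

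The arms could well differ. Session 2 of the app teaches how to monitor and why compliance matters, while controls receive education only at follow-up visits, and the trial is open-label. At stake is whether a reported difference reflects glycaemic control or partly who recorded what.

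**Working it through.** **1. Can the stated check do its job?** Set side by side:

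- What needs testing: the treatment of women lost to follow-up.
- Who is in the check: women who completed the 6-month examination.
- Overlap: none. A woman lost before that examination is excluded by definition.

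This holds whether the assumption referred to is the observed-case rule or, as the sentence order suggests, the rule that lost women count as therapy drop-outs. The section also says that, unless otherwise noted, every analysis is run in both FAS and PP, so the sensitivity analysis adds no new result. Nor is the set well defined: no visit in the schedule is a 6-month visit. The primary endpoint ends at week 12, so a woman with complete primary data could still be excluded for missing a later examination.

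**2. How many women?** The plan's figure reproduces: 80 / (1 − 0.20) = 100 per group, so 20 of 100 per arm are expected to be lost. If their mean in-range percentage is g points below that of the 80 observed, the arm's mean is overstated by 0.20 × g. For g = 10, 20 and 30 (assumed) that is 2, 4 and 6 points. This is the upper case, in which lost women contribute no readings. Only the net difference between arms biases the comparison; equal loss and equal g in both arms cancel.

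**3. Missed readings.** Two days a week for 12 weeks is 24 fasting readings, or 24 × 7 = 168 with the full daily profile. Let p be the true in-range share, and m_in and m_out the shares of in-range and out-of-range readings missed:

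observed share = p(1 − m_in) / [p(1 − m_in) + (1 − p)(1 − m_out)]

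The documents give no miss rates, so all of these are assumed. Example: p = 0.70, m_in = 0.10, m_out = 0.30 gives 0.63 / (0.63 + 0.21) = 0.75. Bias is intervention minus control, in points, with equal true control in both arms and 5% of all readings missed in the other arm:

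| True p, both arms | Control misses 10% in / 30% out | Control misses 5% in / 15% out | App arm misses 10% in / 30% out |
|---|---|---|---|
| 60% | −5.9 | −2.6 | +5.9 |
| 70% | −5.0 | −2.3 | +5.0 |
| 80% | −3.7 | −1.7 | +3.7 |

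Under the first pattern a true gain of 10 points from those control levels appears as 4.1, 5.0 and 6.3. If missingness is unrelated to glucose, the bias is 0 even at 5% versus 25% missed. If both arms follow the 10% / 30% pattern, the bias under no effect is 0 and a true 10 points appears as 9.1, 8.7 and 8.3. The range is not a bound: 10% / 50% in controls gives −13.0, −10.8 and −7.8.

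**4. Effect on the test.** No SD is stated. The SD that returns 80 per group at 10 points, 80% power and one-sided 0.05 is 0.10 × √(80/2) / (1.645 + 0.842) = 0.254. The standard error of the difference is then 0.254 × √(2/80) = 0.040. A 5-point dilution cuts power from 80% to 34%. A 5-point inflation with no true effect raises the one-sided error rate from 5% to 34%.

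**5. Would a tipping-point analysis reach this?** Suppose a share M of an arm's readings is missing, and their in-range share lies δ below the observed one. The arm's full percentage is then observed − M × δ. In the example above, M = 0.70 × 0.10 + 0.30 × 0.30 = 0.16, and the in-range share among missed readings is 0.07 / 0.16 = 43.75%. So δ = 75 − 43.75 = 31.25, and 0.16 × 31.25 = 5.0 points, which is the bias. Varying δ by arm shows how large it must be before the conclusion changes.

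**The case against.** Several points on the other side are sound.

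- A reader might infer that the app prompts or drives glucose testing. The documents do not say so. The clock-in tracks exercise and eating, and the feedback that "will provide positive and constructive feedback to participants to enhance adherence" is not tied to glucose readings. What stands is that session 2 teaches monitoring and compliance to one arm only.
- A reader might infer that the plan expects the arms to differ in missed monitoring because it is a secondary outcome. It is listed without direction, and the stated hypotheses do not name it.
- Missing data are not simply ignored. They are chased by telephone and queried, and missed monitoring is reported. But no analysis rule covers what stays missing.
- Who picks the examination days is a detail an article may leave to the full protocol, and so are the particulars of a missing-data model. However, this article does not leave the matter open: it fixes the rule and the check and excludes other analysis. The exclusion may have been meant for subgroup or exploratory work, but the text sets no such limit.
- A reader might infer a bias as large as the target. With 75% truly in range, 30% of readings missed and out-of-range readings three times as likely to be missed, one arm is inflated by 10.7 points. That is the inflation of one arm under an extreme assumption, not a between-arm difference.

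**Conclusion.** The point holds in two parts of different strength. From the text alone, the completer-only analysis cannot test the handling of women lost to follow-up, and the plan as written permits no other check, with 20% attrition expected. This needs no assumption.

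The effect of missed readings on the primary comparison is conditional. It requires missingness that depends on the glucose value and does so differently by arm. Under the moderate assumed miss rates above, the bias is about 2 to 6 points in either direction against a 10-point target; without dependence on glucose it is zero. The documents settle neither its presence nor its direction. That is why a check able to detect it should be in the plan. The change should be made, but the point does not show that the primary result will be wrong.

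**What to change.** In *Statistical methods for primary and secondary outcomes*:

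1. Keep every randomised woman with any recorded reading in the primary estimate. This affects the definition of the full analysis set, which must be worded to match.
2. Replace the PP-only sensitivity analysis with an arm-specific tipping-point (delta-shift) analysis. It should cover women lost to follow-up, including those with no reading, and missed readings among women who remain. State the range of shifts in advance and report the shifts at which the conclusion changes.
3. Remove the bar on additional analysis as far as it applies to missing data.
4. Report scheduled versus obtained readings by arm and period.
5. If the PP set is kept for another purpose, tie it to a visit that exists in the schedule.

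Two cautions. A mixed model or ANCOVA on recorded readings does not by itself remove value-dependent missingness, so it does not replace step 2. Counting missed readings as out of range may be shown as one bound but is not conservative: with 75% true control in both arms and 5% (app) versus 20% (control) missed at random, it gives 0.75 × 0.95 = 71.25% versus 0.75 × 0.80 = 60%, a spurious 11.25 points for the app.

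The cost is a wording change and a little more analysis on data already collected.

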### Oversight and monitoring

#### Composition of the coordinating center and trial steering committee

Design and conduct of the study: preparation of protocol and amendments; preparation of IB (investigators brochure) and CRFs (case report forms); reports on studies to be published; composition of TMC’s members.

SC (steering committee): final protocol agreement; patient recruitment and communication with the lead investigator; reviewing the trial’s progress and, if necessary, consenting to adjustments to the protocol and/or investigators brochure to help the study run smoothly. The steering group will include all principal investigators. A regional coordinator will be chosen from among the principal investigators at each site.

Trial Management Committee (TMC) (principal investigator, research physician, administrator): study planning; organization of steering committee meetings; report of adverse events to the Chinese National Adverse Reaction Monitoring Center; responsible for the trial master file; budget management and contractual difficulties with individual centers, randomization; data verification. TMC will examine the 12 monthly feedback forms and schedule site visits; data manager: data entry and maintenance of the trial’s IT system; data verification.

Lead investigators: recruitment; data collection; CRF completion, as well as study patient follow-up and adherence to the study protocol and IB. A lead investigator will be assigned to each participating center and will be responsible for patient identification.

#### Adverse event reporting and harms

The type and frequencies of any adverse event will be reported to the Chinese National Adverse Reaction Monitoring Center.

#### Frequency and plans for auditing trial conduct

Audit procedures will comply with the ICH GCP (Guideline for Good Clinical Practice of the International Conference on Harmonisation) and regulatory requirements. The biannual audit was conducted by the ethics committee of the hospital, and the audit process was independent of the sponsor. The steering committee will determine any revisions of the protocol. The amended protocol will also be submitted to the Medical Ethics Committee of the Sir Run Run Shaw Hospital of Zhejiang University and reported to the participants as necessary.

The findings of the study will be presented to the public at academic conferences. The steering group will decide on authorship. The order of the authors will be determined by the contributions of each member.

## Discussion

This article presents a detailed description of a parallel, randomized control trial, designed to evaluate the effectiveness of CBT to reduce hyperglycemia in GDM patients. Lifestyle intervention is recommended as the first-line treatment for GDM per guidelines. To accomplish the primary goal of controlling blood glucose, we consider the mobile-based CBT intervention as an available and accessible method with regard to how to promote healthy habits, and as a result, this will potentially lower blood glucose in ASCVD patients. We believe that mobile-based CBT lifestyle intervention will be potentially effective in lowering blood glucose levels in ASCVD patients.

This study has some critical implications. The novel mobile-based lifestyle intervention is expected to reduce glucose level at a population level due to the high accessibility and availability of technologies. Moreover, this study can potentially demonstrate CBT-based lifestyle intervention’s efficacy in infant outcomes and be utilized as a future guidance for lifestyle intervention in GDM patients.

There are some limitations of this study. First, this study excludes pregnant women whose past medical history include diabetes and only investigates women developing diabetes after diabetes. Future studies could involve a larger patient group. Second, it is impossible to blind participants and staff (excluding statistician) in psychotherapy studies due to the nature of the research. As a result, therapy expectancy effects may be a source of bias.

## Trial status

Protocol version: original; version 1.1 20,210,920.

Recruitment start date: October 1, 2021.

Anticipated completion of recruitment: November 1, 2021.

## Data Availability

The data generated by the study will eventually belong to the study team. If the subjects are infringed due to data disclosure in the trial, the research team will provide them with appropriate compensation if necessary.

## Abbreviations

CBT: Cognitive behavioral therapy
CRC: Clinical research coordinator
CRFs: Case report forms
DM: Data manager
DRD: Diabetes-related distress
DSM-5: Diagnostic and Statistical Manual of Mental Disorders
FAS: Full analysis set
GDM: Gestational diabetes mellitus
GSEs: GENERAL Self-Efficacy Scale (GSEs)
HbA1c: Hemoglobin A1c
IB: Investigators brochure
ICH GCP: Guideline for Good Clinical Practice of the International Conference on Harmonisation
MeSH: Medical Subject Headings
SC: Steering committee
SPIRIT: Standard Protocol ItemsRecommendations for Interventional Trials
T2DM: Type 2 diabetes mellitus
TMC: Trial management committee
